### Comorbidity burden

We will collect information on comorbid disease from participant interview, hospital medical records including primary care records. Comorbidity burden will be calculated using the updated weighting of the Charlson Comorbidity Index^39 40^ and Elixhauser Comorbidity Index.^41^

### Clinical covariates

Vital observations, including blood pressure, heart rate, oxygen saturation, temperature and respiratory rate will be extracted from ORCHARD-EPR.^13^ Participants will be asked to rate their pain using a 10-point pain scale and the Wong-Baker FACES pain rating scale.^42^ The Malnutrition Universal Screening Tool^43^ is used to determine the risk of malnutrition, pressure sore risk is measured using the Braden Scale^44^ and falls risk is assessed using standard hospital protocol by the clinical care team.

### Blood biomarkers

We will extract baseline routine laboratory results (eg, white cell count, neutrophil/lymphocyte ratio, C reactive protein (CRP) level, microbiology) from ORCHARD-EPR.

Additional research blood samples (approximately 20 mLs) are collected for blood banking and storage at −80°C as follows:

Cytodelics-stabilised whole blood for flow cytometry.Whole blood (one 1.5 mL and three 500 µL samples).Buffy coat.EDTA plasma (three 500 µL samples).Lithium-heparin plasma (three 500 µL samples).Serum (three 500 µL samples).Tempus blood RNA tube.

Future biomarker analyses will include:

Flow cytometry for differential immune cell counts and feature characteristics.Cytokine panel (n ~40, eg, Luminex assay).CNS markers (plasma amyloid, τ, neurofilament light chain, glial fibrillary acidic protein, serum 100 beta protein, neurogranin).Proteomics (eg, Olink, ~5000 proteins).Transcriptomics.DNA extraction and Apolipoprotein E genotyping.

Blood sampling is performed at baseline and at each follow-up visit.

### Neuroimaging biomarkers

Brain imaging (CT or MRI scan) completed as part of routine clinical care during the index admission or previous clinical encounters is obtained from the hospitals’ Picture Archiving and Communication System and pseudonymised (deidentified) for analysis. For participants who do not have existing brain imaging, a research CT-brain scan is performed. Participants from OUHFT requiring a research scan undergo brain imaging using the Acute Multidisciplinary Imaging and Interventional Centre photon-counting CT-(PCCT) scanner situated in the John Radcliffe Hospital, Oxford, whereas RBFT participants have a standard CT-brain scan. Incidental findings are communicated to participants as soon as possible and to their general practitioners and relevant clinical teams with the participants’ permission.

We will quantify the severity of brain atrophy and white matter disease using validated visual rating scales including the Global Cortical Atrophy Scale^45^ and the Fazekas^46^ and/or Age-Related White Matter Changes Scale.^47^ The presence of other brain lesions (eg, stroke or tumour) will be recorded.

### Follow-up assessments (3-month, 1-year and 3-year)

Participants are followed up in-person at the research clinic or by home visit or telephone if necessary. A structured proforma similar to the baseline assessment proforma is used, including information on health condition, frailty, residence and care needs. We also collect information on any intervening hospital admissions or attendance at memory or falls clinics. A brief clinical examination measuring pulse, blood pressure (and postural blood pressure) is performed. The IQCODE and NPI-Q will be repeated at 3-year follow-up.

Indirect follow-up using ORCHARD-EPR^13^ (which includes linked mental health hospital records) and hand searching of medical records including primary care records via the hospital EPR portals will be used to mitigate loss-to-study-interview follow-up. Data on all-cause mortality will be obtained from the Office of National Statistics.

#### Cognitive assessments at follow-up

Cognitive assessments including AMTS, 4AT, MoCA and Mini Mental State Examination^48^ will be undertaken. Additional cognitive testing including a short Neuropsychological Battery Test is done tailored to participants’ ability including the Boston Naming Test,^49^ Hopkins Verbal Learning Test,^50^ Rey Figure Copy,^51^ Symbol Digit Modalities Test,^52^ Trail Making Test A and B^53^ and Semantic Fluency.^54^

#### Physical function

ADL are assessed using the mRS and Barthel Index. Additionally, participants complete the Nottingham ADL scale^55^ and the Timed Up and Go test.^56^

#### Quality of life and mood

Participants complete the EuroQol-EQ-5D-3L^57^ to measure quality of life and the Geriatric Depression Scale to screen for depression.^58^

#### Participant evaluation questionnaire

A mixed quantitative and qualitative questionnaire is administered at 3-month follow-up and will be repeated at the 3-year follow-up (see online supplemental file 1). Participants are asked about their experience of cognitive assessments in hospital, whether they would wish to be informed of their dementia risk in future according to any risk prediction algorithms in development, and their preferred method of being advised on brain health and dementia risk (eg, informed by hospital staff vs general practitioners vs via written information only).

### Outcome measures

The outcome measures include:

Length of stay defined as day of admission to day of discharge from OUHFT and RBFT acute care.Change in care needs defined as change in frequency of care package or number of carers (single-handed vs double-handed), discharge to community hospital or rehabilitation unit or new discharge to care home or nursing home.Institutionalisation defined as new permanent placement at care home or nursing home.Mortality during admission or during follow-up period. We will also record cause of inpatient death.Readmission to hospital within 30 days of discharge.New dementia diagnosis and subtype (Alzheimer’s disease, vascular dementia, mixed, Parkinson’s disease dementia, Lewy body dementia or other).Longitudinal change in cognition and functional status.

Table 1 summarises the data collected prospectively at baseline and at follow-up (3 months, 1 year and 3 years).

### Linkage to ORCHARD-EPR

Baseline and follow-up participant interview data will be supplemented through linkage to ORCHARD-EPR.^13^ ORCHARD-EPR contains structured information from assessments performed by the healthcare team as part of standard care including nursing risk assessments (falls risk, nutrition, pressure sore risk, frailty), cognitive assessments (10-point-AMTS, CAM,^15^ 4A’s test-4AT,^16^ MoCA), observations, laboratory test results and hospital administrative information including ICD-10 diagnostic and procedure coding and outcomes including length of stay, discharge destination and mortality. Derived variables include illness severity (systemic inflammatory response syndrome-SIRS, National Early Warning Score-NEWS2)^59 60^ and the Hospital Frailty Risk Score.^61 62^

### Statistical analyses

Demographic data will be summarised using descriptive statistics and comparison between delirium versus no delirium groups will be performed using the χ^2^ test for categorical data and t-test/analysis of variance for continuous data. The prevalence and incidence of delirium, including the subtype (hypoactive, hyperactive, mixed), and the severity and duration of delirium will be determined together with the prevalence of preadmission dementia diagnosis and incidence of new dementia diagnosis on follow-up including the subtype. Logistic regression will be used to determine the associates of delirium (any, and by subtype and severity) adjusted for covariates including demographic factors, infection, illness severity, baseline cognition, frailty and comorbidity and apolipoprotein E genotype.

Cox proportional hazards regression will be used to determine the HRs for new dementia on follow-up in participants with versus without delirium, adjusted for covariates as above and stratified by baseline brain imaging factors (small vessel disease, atrophy). Longitudinal cognitive data from all time points will be used to examine the evolution of cognitive impairment over time including in specific cognitive domains. Free text responses in the evaluation questionnaire will undergo thematic analyses to determine participants’ experience and understanding of the rationale for performing cognitive tests in hospital, and their perspectives on being informed about their brain health and the risk of developing dementia in future based on information collected in their hospital records.

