### Sample size

The sample size required to determine the independent associates of delirium and incident dementia is based on the rule of 10 outcomes per predictor. With the assumption of 10 independent predictors of delirium, 100 cases of delirium are required. Assuming five independent predictors of incident dementia, at least 50 dementia cases are required by end of 3-year follow-up. One previous study among general medical patients found a dementia occurrence of 60% in those with delirium over a median follow-up of 32.5 months (18.1% per year).^11^ Therefore, 83 people with delirium without dementia at baseline are required for our study. It is estimated that around half of patients with delirium have underlying dementia (with or without prior formal diagnosis),^12^ hence we would require 166 (83×2) patients with delirium at baseline. Based on our previous work showing a delirium occurrence of 30% in acute medicine patients aged >65 years, we will require an overall cohort size of 553 patients.^2^

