### Delirium ascertainment

Delirium diagnosis is made by the principal investigator ([name]) in discussion with the research team at weekly lab meetings and after review of all study records, clinical records and information from informants in accordance with the DSM-V criteria. Participants who have some but not all of the DSM-V criteria are classified as subsyndromal delirium.

Delirium is defined by onset time as described previously^2^:

Prevalent: present on or within 48 hours of admission;Incident: developing at least 48 hours after admission;Any: presence of prevalent or incident delirium.Both: where patients with prevalent delirium have a further episode of incident delirium at least 48 hours after resolution of the previous delirium episode.

The duration of delirium is defined as the day of delirium diagnosis to the day of full resolution. Motor subtype is characterised as hypoactive, hyperactive or mixed. The aetiology of delirium is determined and may include one or more of infection, constipation, dehydration, medication, pain, new intracerebral event or other. The presence of pre-existing dementia diagnosis is used to classify delirium as delirium only versus delirium superimposed on dementia.

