### CNS biomarkers

The cognitive impact of delirium extends beyond the immediate period of acute illness and is associated with long-term cognitive decline. Several mechanisms are thought to contribute to neuronal injury or damage, including neuroinflammation, altered brain energy metabolism including impaired glucose utilisation^68^ or activation of the kynurenine pathway with increased levels of neurotoxin quinolic acid.^69^ Examining biomarkers of neuronal function in alignment with The National Institute on Aging-Alzheimer’s Association biological construct of ATN biomarkers for Alzheimer Disease and related dementias may help inform underlying brain vulnerability including the presence of pre-existing neurodegeneration and subsequent dementia risk. Delirium has been associated with such biomarkers,^70 71^ but there remains uncertainty whether this simply indicates the presence of pre-clinical dementia or whether delirium initiates an acute neurodegeneration process. Recently, neurofilament light chain (a marker of neuronal injury) was shown to increase in acute illness and be persistently elevated at follow-up, suggesting precipitation of neuronal damage.^71^ Interestingly, neurofilament changes were greatest in those with a better cognitive baseline consistent with previous studies demonstrating greater cognitive impacts of delirium in those with good cognition.^5 71 72^ In other studies, S100Beta (a marker of blood–brain barrier permeability) has shown conflicting associations with delirium.^73^

It has been proposed that there are distinct pathophysiological pathways underlying delirium aetiologies and subtypes linked to diverse predisposing and precipitating factors (eg, infection, dehydration, liver failure, hypoxia, medication). However, there are few existing studies comparing biomarker profiles between delirium subtypes, and in most, sample sizes are too small for meaningful analysis.

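### The subtype analysis of delirium names logistic regression by subtype but no contrast between subtypes, so for modest shared effects separate models can look subtype-specific when nothing differs

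*Protocol article*

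**What the plan says.** The Statistical analyses section states: "Logistic regression will be used to determine the associates of delirium (any, and by subtype and severity", with adjustment for covariates. It names no reference group for the subtype models, no multinomial model and no between-subtype test.

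The Delirium ascertainment section defines the classes: "Motor subtype is characterised as hypoactive, hyperactive or mixed". Together with no delirium, this is a nominal outcome with four levels.

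The Introduction criticises earlier work for reducing delirium to present or absent, and says that the biomarker profile of different delirium characteristics is unknown. The CNS biomarkers section of the Discussion reports the proposal that "there are distinct pathophysiological pathways underlying delirium aetiologies and subtypes linked to diverse predisposing and precipitating factors", and adds that "there are few existing studies comparing biomarker profiles between delirium subtypes, and in most, sample sizes are too small for meaningful analysis".

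The Sample size section is "based on the rule of 10 outcomes per predictor" and covers any delirium and incident dementia. It has no figure for a single subtype.

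**The concern.** Whether biomarker profiles differ between hypoactive, hyperactive and mixed delirium is a question of comparison. Its null hypothesis is that a marker has the same association with all three. A model fitted for one subtype tests another null, that the marker has no association with that subtype. Three such tests, each against zero, do not test whether the three coefficients differ.

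A binary model for one subtype must also either count patients with the other subtypes as non-cases or leave them out. The two choices estimate different odds ratios.

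The subtypes will be small and probably unequal. A marker with one common effect can then reach significance in the largest group and miss it in the others through precision alone. If that pattern were reported as a subtype-specific profile, the study would repeat the small-sample weakness that its Discussion finds in earlier work.

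**Working it through.** **1. The plan's own numbers (Sample size section).** 10 predictors × 10 = 100 delirium cases. 5 × 10 = 50 dementia cases. 50 / 0.60 = 83.3, taken as 83. 83 × 2 = 166 delirium cases. 166 / 0.30 = 553.3, taken as 553. The stated cohort is reproduced, and 553 − 166 = 387 patients have no delirium. Three subtypes share 166 cases, an average of 166 / 3 = 55.3.

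**2. Assumptions not in the article.** Two-sided 5% level; a marker scaled to unit SD; the same odds ratio (OR) per SD in every subtype; each subtype compared with the 387; no covariate adjustment; splits of 55.3/55.3/55.3, 83/41.5/41.5 and 100/33/33.

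**3. Formulae.** For subtype k with n_k cases, the log odds ratio has standard error about √(1/n_k + 1/387). The three estimates share their controls, with covariance 1/387. The equality test is Q = Σ n_k (b_k − b̄)², where b̄ is the mean weighted by n_k. It is compared with 5.99 (chi-square, 2 df). The error from the shared controls cancels.

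**4. One case in full: OR 1.3, split 83/41.5/41.5.** log 1.3 = 0.262.
- Largest subtype: SE = √(1/83 + 1/387) = 0.121, z = 2.17, power about 58%.
- Each smaller subtype: SE = √(1/41.5 + 1/387) = 0.163, z = 1.61, power about 36%.
- Simulating the three correlated estimates: all significant 10%, none 20%, mixed 70%.

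**5. Chance of a mixed pattern when the effect is identical in all subtypes** (normal approximation by simulation)

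| OR per SD | 55.3/55.3/55.3 | 83/41.5/41.5 | 100/33/33 |
|---|---|---|---|
| 1.0 | 14% | 14% | 14% |
| 1.1 | 26% | 26% | 26% |
| 1.2 | 52% | 52% | 53% |
| 1.3 | 68% | 70% | 73% |
| 1.4 | 63% | 68% | 74% |
| 1.5 | 44% | 52% | 62% |
| 1.75 | 8% | 14% | 24% |
| 2.0 | 1% | 2% | 6% |

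The equality test rejects in about 5% in every cell.

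**6. Checks.**
- Individual-data simulation (600 data sets per scenario, equal and 50/25/25 splits) gave mixed patterns in 67–68% at OR 1.3, 42–49% at 1.5 and 1–4% at 2.0. The 2-df Wald test from one multinomial model rejected in 4.3–5.5%.
- A more uneven split (60/10/30) raises the peak to 79% at OR 1.4, and gives 21% at OR 2.0.
- If covariate adjustment inflates the variances by 1.5, the pattern moves to larger effects. Over four splits from equal thirds to 60/10/30 it is 42% at OR 1.2, 64–79% at 1.5 and 7–40% at 2.0.

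**The case against.** The strongest reply is that the article does not fix the faulty method.
- Multinomial and ordinal models are also logistic regressions. The same phrase covers severity, which is measured on graded scales, so it may be shorthand for a family of models.
- The Aims and objectives section lists biomarker associations with delirium and dementia, not differences between subtypes. The subtype question appears only as background and discussion. A model per subtype does answer which factors are associated with each subtype.
- A condensed article commonly leaves reference groups and contrasts to a fuller plan, which is not shown here.

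Much of this stands. Separate models are an inference, though the natural one, since the phrase sets subtype beside the binary outcome of any delirium. A reader might also infer that the plan will declare distinct subtype pathways whenever significance differs between subtypes. The article does not support that: it gives no significance rule and no criterion for a subtype-specific claim, and odds ratios with confidence intervals per subtype would satisfy its wording equally well.

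What remains is a mismatch. The article gives a method for subtypes, and that method as worded does not address the comparison that it presents as the gap.

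**Conclusion.** The point holds in a limited form. As worded, the subtype analysis most naturally tests each subtype against zero and includes no test of whether subtypes differ. For a shared effect of OR 1.2 to 1.5 per SD, separate models would give a mixed significance pattern in about 44% to 74% of studies of the planned size, against about 5% false rejections for a direct equality test.

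That range is unadjusted and depends on an assumed 5% level and assumed splits between equal thirds and 100/33/33. The article gives neither subtype frequencies nor expected effect sizes. It would be tempting to say that a shared effect will usually look subtype-specific. That is too broad: under the same assumptions the figure is 14% with no effect, 26% at OR 1.1 and 1% to 6% at OR 2.0. The cohort size of 553 is not in question.

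**What to change.** In the Statistical analyses section, replace the subtype part of the sentence with:
- one multinomial logistic model with no delirium as reference and hypoactive, hyperactive and mixed as the other classes, using the planned covariates;
- for each marker, a Wald or likelihood-ratio test that its three coefficients are equal, with pairwise ratios of odds ratios and 95% confidence intervals;
- a statement that a subtype-specific profile is claimed only from that contrast.

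The model should not be carried over to aetiology groups. The Delirium ascertainment section lets a patient have more than one cause, so those groups are not mutually exclusive.

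The change needs no new data. The biomarker assays are described as future work and in-person follow-up runs to February 2028, so the wording can be settled before those results exist.

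The cost is that imprecision becomes visible, because the model adds no cases. With an 83/41.5/41.5 split, the largest-against-smaller contrast has SE √(1/83 + 1/41.5) = 0.190. Its 95% interval therefore runs from the estimate divided by 1.45 to the estimate times 1.45, since exp(1.96 × 0.190) = 1.45. For 33 against 33, SE = √(2/33) = 0.246 and the factor is 1.62. Fewer subtype claims will be made.

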### Patient and public involvement

Our patient and public involvement (PPI) group includes patients with lived experience of cognitive frailty and acute hospital admission, carers, a retired general practitioner and members of the Alzheimer’s Society. The PPI group previously highlighted the need for studies to inform the development of delirium treatments and for better information for patients and carers on the prognosis of delirium, particularly in identifying those at higher risk of developing dementia. Group members provided input into the ORCHARD-PS protocol, the evaluation questionnaire and study design including around potential logistical challenges for patients returning for follow-up assessments at the hospital. The protocol therefore includes the option of telephone and home visit follow-up where required. Going forward, the PPI group will inform the conduct, outcome selection, reporting and dissemination of the study.

## Discussion

### Summary

ORCHARD-PS is a bi-centre, observational study of the impact of acute illness and delirium on cognitive health and future dementia risk including detailed characterisation of delirium and collection of clinical, blood and neuroimaging biomarkers. Data are collected from a range of sources, including direct assessment and interview with participant or informant supplemented by electronic medical record linkage and hand searching of records. ORCHARD-PS focuses on older hospital patients who are most vulnerable to delirium and includes people across the frailty spectrum who are generally under-represented in research.^63^ Through the use of multimodal biomarkers, ORCHARD-PS will advance our understanding of delirium pathophysiology necessary to develop new treatments and the underpinning mechanisms linking delirium and acute illness to future dementia.

### Biomarkers of the systemic response

Acute illness induces inflammatory, immunologic and other systemic responses, which are thought to precipitate delirium in many cases. It is hypothesised that peripheral inflammatory cytokines cross the blood–brain barrier and trigger an inflammatory cascade in the brain, resulting in neuronal injury and cognitive dysfunction.^64 65^ Inflammatory mediators are the most frequently studied biomarkers in delirium, particularly IL-6, CRP, tumour necrosis factor-α and IL-1β, although results are conflicting possibly owing to differences in patient populations, small sample sizes and adjustment for confounders.^10 66^ Most studies are focused on surgical or critically ill patients, with limited data from older acute medical inpatients^67^ where inflammatory biomarker profiles may vary with different predisposing and precipitating factors.

### CNS biomarkers

The cognitive impact of delirium extends beyond the immediate period of acute illness and is associated with long-term cognitive decline. Several mechanisms are thought to contribute to neuronal injury or damage, including neuroinflammation, altered brain energy metabolism including impaired glucose utilisation^68^ or activation of the kynurenine pathway with increased levels of neurotoxin quinolic acid.^69^ Examining biomarkers of neuronal function in alignment with The National Institute on Aging-Alzheimer’s Association biological construct of ATN biomarkers for Alzheimer Disease and related dementias may help inform underlying brain vulnerability including the presence of pre-existing neurodegeneration and subsequent dementia risk. Delirium has been associated with such biomarkers,^70 71^ but there remains uncertainty whether this simply indicates the presence of pre-clinical dementia or whether delirium initiates an acute neurodegeneration process. Recently, neurofilament light chain (a marker of neuronal injury) was shown to increase in acute illness and be persistently elevated at follow-up, suggesting precipitation of neuronal damage.^71^ Interestingly, neurofilament changes were greatest in those with a better cognitive baseline consistent with previous studies demonstrating greater cognitive impacts of delirium in those with good cognition.^5 71 72^ In other studies, S100Beta (a marker of blood–brain barrier permeability) has shown conflicting associations with delirium.^73^

It has been proposed that there are distinct pathophysiological pathways underlying delirium aetiologies and subtypes linked to diverse predisposing and precipitating factors (eg, infection, dehydration, liver failure, hypoxia, medication). However, there are few existing studies comparing biomarker profiles between delirium subtypes, and in most, sample sizes are too small for meaningful analysis.

